## Abstract

**Background:**

Stroke is one of the most frequent causes of death and disability worldwide. It is accompanied by the impaired motor function of the upper extremities in over 69% of patients up to hemiplegia in the following 5 years in 56% of cases. This condition often is characterized by chronic poststroke pain, difficult to manage, further worsening quality of life. Poststroke pain occurs within 3–6 months. Robot-assisted neurorehabilitation using the Automatic Recovery Arm Motility Integrated System (ARAMIS) has proven efficacy in motor function recovery exploiting the movements and the strength of the unaffected arm. The rationale of the ROBOCOP (ROBOtic Care of Poststroke pain) randomized trial is the assessment of the impact of robot-assisted functional and motor recovery on the prevention of poststroke pain.

**Methods:**

A total of 118 patients with hemiplegic arms due to stroke will be enrolled and randomly allocated with a 1:1 ratio to ARAMIS or conventional neurorehabilitation group. After a baseline screening at hospital discharge, ARAMIS or conventional rehabilitation will be performed for 8 weeks. The primary endpoint is the prevention of the development of poststroke pain and the secondary endpoints are prevention of spasticity and efficacy in clinical motor rehabilitation. The primary outcome measures consist in the visual analog scale and the doleur neuropatique 4 and the secondary outcome measures include: the Modified Ashworth Scale, the Resistance to Passive movement Scale; the Upper Extremity Subscale of the Fugl–Meyer Motor Assessment; the Action Research Arm Test; the Barthel Index for activities of daily living; and the magnetic resonance imaging (MRI) recovery-related parameters. After baseline, both primary and secondary outcome measures will be performed in the following time points: 1 month after stroke (*t*_1_, half of the rehabilitation); 2 months after stroke (*t*_2_, after rehabilitation); and 3 months (*t*_3_) and 6 months (*t*_4_) after stroke, critical for poststroke pain development.

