### Eligibility Criteria

Consecutive patients, admitted to Sant' Anna Institute with the diagnosis of stroke after hospital discharge will be enrolled, accordingly with the following inclusion criteria:

- First-ever stroke within 24–72 h from diagnosis confirmed through functional MRI scan, regardless of the side, location, and extension of the lesion;-Stroke-related hemiplegic patients of any age at hospital discharge within 48–72 h after stroke with fMRI scan of the area affected;-Severe upper limb impairment, according to the Upper Extremity Subscale of the Fugl–Meyer Motor Assessment [FMA-UE (0-35) (21)];-Absence of hemiplegic upper limb-related baseline pain based on the visual analog scale (VAS), the bedside active examination with a numerical rating and, also, the douleur neuropathique en 4 questions (DN4) for the evaluation of neuropathic prestroke pain.

Exclusion criteria will be:

-Bilateral impairment;-Presence of aphasia;-Presence of cognitive impairment, as assessed using the cognitive assessment scale for patients with stroke (22), to avoid interference of aphasia or hemispatial neglect that may occur with the commonly used Mini-Mental State Examination (23) and Montreal Cognitive Assessment (24);-Stroke diagnosis without the occurrence of hemiparesis of the upper limb;-Previous rehabilitation.

Due to the lack of specific observational tools for poststroke pain in noncommunicative patients, this pilot study will not include patients affected by aphasia and cognitive impairment. The informed consent will be obtained by healthcare operators and patients will be informed about the study and they will be provided with a consent form. No additional consent provisions for biological specimens will be needed since the latter will not be collected.

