### Outcomes

The effect of robot-assisted rehabilitation using ARAMIS on the prevention of the development of poststroke pain is the primary endpoint of the ROBOCOP study. The primary outcome measures consist in the assessment of pain through the VAS, including a bedside active examination and probing of somatosensory functions to test touch, temperature, and pain sensations (26). The development of neuropathic components of poststroke pain will be assessed using the DN4. The secondary endpoints include spasticity, tightly linked to pain and developed by up to 40% of patients with hemiparetic stroke, and clinical motor rehabilitation. Spasticity will be assessed using the Modified Ashworth Scale (MAS) (27) and the Resistance to Passive movement Scale (REPAS), based on the Ashworth scale (28), for major joint movements in upper and lower limbs. Clinical motor rehabilitation will be measured according to the Standardizing Measurement in Arm Rehabilitation Trials [SMART] toolbox of the recommended core set of outcome measures for rehabilitation after stroke (29, 30). The latter includes FMA-UE, the Action Research Arm Test, and the activities of daily living/stroke-specific outcomes of the Barthel Index. The clinical motor rehabilitation will also be characterized through structural and functional MRI scan. In particular, structural MRI is intended to evaluate infarct and injury volume (31) and functional MRI to assess the activation volume in the stroke ipsilateral hemisphere during movement of paretic limb, which is related to the extent of behavioral recovery (32). The connection strength between the ipsilesional primary motor cortex and the contralateral regions will be examined (33).

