### Participant Timeline

Patients will be randomly allocated to the intervention or control group in a 1:1 allocation ratio. The enrollment will last up to the achievement of the sample size. The most important time points for the assessment of pain development are 3 and 6 months poststroke, with the addition of measurement time points in the subacute phase (29, 34). In fact, differences in motor activity of paretic limbs 24–36 h after symptoms onset, and also at 3 and 6 months (35, 36) have been demonstrated. Therefore, the assessment of the primary and secondary outcomes will be conducted at the following time points: baseline measurement at Sant'Anna Institute admission (24–72 h since stroke event) (*t*_0_); 1 month after stroke (*t*_1_), i.e., at half of the rehabilitation period; 2 months after stroke (*t*_2_), i.e., after the completion of neurorehabilitation with ARAMIS in the intervention group and of conventional rehabilitation in the nonintervention group; 3 months (*t*_3_) and 6 months (*t*_4_) after stroke, since the latter are critical for rehabilitation and pain development. Routine clinical and neurophysiological assessments will be performed before and at the end of the treatment. Loss of tolerance to the procedure up to discontinuation will be recorded on a specific form. The schedule of enrollment, interventions, and assessments is reported in Table 1.

**Table 1 T1:** Schedule of enrollment, interventions and assessments according to Standard Protocol Items: Recommendations for Interventional Trials (SPIRIT).

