### Statistical Analysis

The statistical analysis plan follows the Consolidated Standards of Reporting Trials (CONSORT) evidence-based reporting guideline to ensure research transparency, specifically to trials of nonpharmacologic treatments (NPTs), as rehabilitation (48). The primary (pain) and secondary (spasticity and rehabilitation parameters) outcome measures, collected at prespecified time point *t*_3_ and *t*_4_ vs. *t*_0_, will be expressed as mean and standard error and assessed for statistically significant differences using independent *t*-test for data normally distributed or Mann–Whitney U test for skewed data. Based on the CONSORT NPT item 12b, the evaluation of the outcome measures over time will be carried out through a linear mixed model. The correlation between pain (VAS measure) and recovery (FMA-UE), assessed at *t*_0_, *t*_1_, *t*_2_, *t*_3_, and *t*_4_, will be performed through the Pearson product-moment correlation coefficient (*r*). In agreement with the CONSORT NPT item 12a, the clustering of data will be performed by blinded care providers of the center. Statistical analysis will be performed using SPSS statistics software (Chicago, IL, USA). Values of *p* < 0.05 will be considered statistically significant.

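### Prevention of spasticity is named as a secondary endpoint, but the stated analysis compares spasticity severity scores and cannot by itself show that new cases were prevented

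*Protocol article*

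**What the plan says.** The abstract (Methods) states that "the secondary endpoints are prevention of spasticity and efficacy in clinical motor rehabilitation". The Introduction gives a working hypothesis in the same direction: that ARAMIS would avoid spasticity occurring. The Outcomes section is looser and does not use the word prevention: "The secondary endpoints include spasticity, tightly linked to pain and developed by up to 40% of patients with hemiparetic stroke". It then names the instruments: "Spasticity will be assessed using the Modified Ashworth Scale (MAS) (27) and the Resistance to Passive movement Scale (REPAS", the latter covering both upper and lower limbs.

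For pain, the Eligibility Criteria require "Absence of hemiplegic upper limb-related baseline pain based on the visual analog scale (VAS". They contain no corresponding criterion for muscle tone. The inclusion criterion on arm function is "Severe upper limb impairment, according to the Upper Extremity Subscale of the Fugl–Meyer Motor Assessment", which concerns motor impairment.

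The Participant Timeline places the "baseline measurement at Sant'Anna Institute admission (24–72 h since stroke event" and schedules primary and secondary outcomes at t0 and at every later time point. The Statistical Analysis section takes the outcome measures "collected at prespecified time point *t*_3_ and *t*_4_ vs. *t*_0". Each is to be summarised by its mean with standard error, and the arms compared by t-test, or by Mann–Whitney U where the data are skewed. A linear mixed model covers the course over time.

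**The concern.** Prevention is a statement about occurrence: fewer patients who were free of spasticity go on to have it. Supporting it requires a definition of a new case, a group at risk, and a comparison of how many in each arm become cases. The article's stated analysis has none of these. It compares how high the scores are.

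A lower mean MAS with ARAMIS could arise from fewer new cases, from milder new cases, or from improvement in patients who already had raised tone at t0. Only the first is prevention. If the analysis is carried out as described and reported under the abstract's endpoint, a severity result may be presented as a prevention result.

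**Working it through.** The plan gives no figure for this point that could be reproduced, so the check sets claim against analysis and then looks at consequences under stated assumptions.

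**Claim against analysis**

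| Needed for a prevention claim | What the article states |
|---|---|
| Definition of a new case | None; MAS and REPAS are used as scores |
| Patients at risk at t0 | No tone criterion at entry and no subset defined |
| Comparison of occurrence | None; t-test or Mann–Whitney U on scores, plus a mixed model |

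**Can scores differ with no case prevented?** Assume nobody is spastic at t0, 53 patients per arm (the article's evaluable number), and 40% of each arm becoming spastic (the upper figure in Outcomes). Assume every case scores 2 with conventional rehabilitation and 1 with ARAMIS.

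- Difference in new cases: 40% − 40% = 0.
- Means: 0.40 × 2 = 0.8 and 0.40 × 1 = 0.4, a difference of 0.4.
- Variances: 4 × 0.40 × 0.60 = 0.96 and 1 × 0.40 × 0.60 = 0.24.
- Standard error: √[(0.96 + 0.24)/53] = 0.150, so the expected z is 0.4/0.150 = 2.66.
- Normal approximation: the chance of a significant t-test is Φ(2.66 − 1.96) = Φ(0.70), about 76%.

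The Mann–Whitney test is less sensitive to this pattern but also responds to it. A random control patient scores higher than a random ARAMIS patient with probability 0.40, and lower with probability 0.40 × 0.60 = 0.24. With everyone at 0 at t0, change scores equal follow-up scores, so using t0 as the reference alters nothing here.

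**What does raised tone at t0 do?** The article gives no rate, so 0% to 30% is an assumed range. In a simulation with 53 per arm and 2,000 runs per scenario, new spasticity among patients at risk was 40% in controls and 15% with ARAMIS. Cases scored 1, 2 or 3 with equal chance (mean 2), and cases present at t0 stayed unchanged. The expected mean difference is (1 − p) × (0.40 − 0.15) × 2, where p is the share spastic at t0.

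| p | Expected difference | Power, change from t0 | Power, follow-up score alone |
|---|---|---|---|
| 0% | 0.50 | 77% | 77% |
| 10% | 0.45 | 70% | 61% |
| 20% | 0.40 | 64% | 46% |
| 30% | 0.35 | 56% | 34% |

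With no true effect, the rejection rate lay between 4.5% and 6.0% throughout, close to the nominal 5%. Raised tone at t0 dilutes the contrast and costs power; it does not generate false positives. Using t0 recovers part of the loss.

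**The case against.** A reader might infer something stronger: that spasticity already present at t0 counts against the arm as a failure to prevent it, or biases the result. The documents do not support this. No failure or responder category is defined, and t0 is the stated reference. On a change-score reading, a patient with MAS 2 at t0 and 2 at 3 months contributes 0, the same as a patient who never becomes spastic. Pre-existing cases would count as events only under a binary endpoint of being spastic at follow-up, which the article does not state. Even then the contrast would only shrink: with 40% and 30% among those at risk and 20% spastic at t0, the rates are 0.20 + 0.80 × 0.40 = 52% and 0.20 + 0.80 × 0.30 = 44%, a difference of 8 points instead of 10.

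Nor does chance imbalance in t0 tone show a defect. The 95% range, 1.96 × √[2p(1 − p)/53], is 8, 11 and 15 points for assumed p of 5%, 10% and 20%. That is ordinary sampling variation under 1:1 randomisation, which a valid test allows for.

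Three further points deserve weight. First, entry is at 24–72 h after a first-ever stroke without previous rehabilitation, which excludes spasticity left by an earlier stroke; early raised tone may be uncommon, though the article gives no figure. Second, the trial calls itself a pilot and exploratory, spasticity is secondary, and the Outcomes wording fits a score analysis. Third, a cut-off and an at-risk set could sit in a statistical analysis plan that is not shown, so their absence alone is no fault.

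These points limit the concern but do not remove it. The article itself states both the prevention endpoint and the method for the secondary outcomes, and the two do not match, even if nobody has raised tone at t0.

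**Conclusion.** The mismatch stands: a severity comparison on MAS and REPAS, however t0 is handled, cannot by itself support a claim that ARAMIS prevents spasticity. In the worked example the mean score halves with no case prevented; this rests on an assumed 40% in both arms and assumed scores of 2 and 1.

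The effect of raised tone at t0 is loss of sensitivity. Over an assumed 0% to 30%, power falls from 77% to 56% for change scores and to 34% for follow-up scores alone. The true rate is unknown, and at 0% this part disappears. The phrase comparing t3 and t4 with t0 does not settle which of the two readings is meant.

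The point affects how one secondary endpoint may be interpreted, not the validity of the randomised comparison or the primary endpoint. It should be corrected before the data are analysed.

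**What to change.** Leave entry, treatment and visits unchanged.

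1. **Severity:** analyse MAS in the paretic arm at t3 and t4 in all patients, adjusted for the t0 value, and report it as severity.
2. **New spasticity:** among patients without raised tone at t0, compare the proportion with new spasticity in the paretic arm at t3 or t4, using a pre-specified MAS cut-off (for example above 0), as a difference in proportions with a 95% interval. Because the subset is defined by a t0 measurement, the comparison within it remains randomised.
3. **Wording:** reserve prevention for the second result. If an incidence analysis is not wanted, reword the abstract's endpoint to spasticity severity, in line with the Outcomes section.

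The cost is analysis wording only, since MAS at t0, t3 and t4 is already planned. Dichotomising discards the grade of spasticity, and patients with tone at t0 leave the second analysis, so it will generally be less precise than the score analysis. For assumed rates of 40% and 30%, the 95% half-width is 1.96 × √[(0.40 × 0.60 + 0.30 × 0.70)/n]: 18 points with n = 53 per arm, and 20 points with n = 42 if 20% have tone at t0. The interval should be reported with that in mind.

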**Discussion:**

This is the first clinical trial investigating the efficacy of robot-assisted neurorehabilitation using ARAMIS on poststroke pain prevention. This study could remarkably improve the quality of life of stroke survivors.

## Introduction

### Background and Rationale

Stroke represents one of the most serious causes of death and disability-adjusted life-years lost (1) destined to keep increasing due to global aging. One of the most common long-term disabilities occurring in over 69% of cerebrovascular lesions consists of impaired motor function of the upper extremities up to hemiplegia in the following 5 years in 56% of cases (2, 3). Stroke is complicated by the occurrence of poststroke pain usually within 6 months from the acute event (4), with poststroke pain syndromes reported in up to 30%−40% of stroke outliving patients (5), chronic in 11–55% of patients (6). The latter include pain caused by different pathophysiology in which nociceptive and neuropathic features can coexist ranging from pain secondary to spasticity, shoulder pain, complex regional pain syndrome (CRPS), and headache, in 1 out of 10 stroke sufferers, that is, migraine-like in 31.3% cases (7), to central poststroke pain (8). Shoulder pain is the most frequent affecting some 30–40% of stroke survivors (6). Lenticulocapsular strokes can cause hemiparesis with consequent shoulder pain (9). The development of poststroke pain correlates to the severity of stroke and paresis is associated with a 3.1-fold higher risk for stroke-related pain (10). Unfortunately, often patients suffering from pain after stroke do not find relief in current analgesic treatment because it is not supported by clinical trials, as a consequence, guidelines are lacking (9). In fact, the systematic review and meta-analysis of literature has highlighted that very few clinical trials assess the efficacy of opioids, the most potent analgesics on poststroke pain, the number of patients is very small and these studies have not been designed specifically for this condition, thus usually not evaluating the correlation between rehabilitation, pain, and physical functioning after stroke (11). Actually, stroke survivors do not even benefit from clinical trials on the novel preventative treatment of migraine, e.g., the anticalcitonin gene-related peptide monoclonal antibody eptinezumab that can provide rapid and longer-lasting action (12). This is often due to the lack of use of pain scales for an objective pain assessment validated in specific populations, e.g., patients affected by stroke, and this problem becomes even more worrying for patients with aphasia and noncommunicative and in the pandemic emergency (13–16). Robot-assisted neurorehabilitation for patients with stroke having the Integrated Robotic System for Stroke (IRSS) prototype Automatic Recovery Arm Motility Integrated System (ARAMIS) has provided a significant improvement of motor recovery (17). It consists of two computer-controlled, symmetric, and interacting exoskeletons that impress to the paretic arm the same strength and movement of the healthy arm and it has been validated in stroke survivors. The rationale for the use of ARAMIS in poststroke neurorehabilitation of the paretic upper limb relies on the possible prevention of aberrant early plasticity. According to our working hypothesis, ARAMIS might improve plasticity in agreement with the concept underlying the Reinforcement-Induced Movement Therapy (18), avoiding the occurrence of spasticity and hypotonia.

### Objectives

In agreement with the Initiative on Methods, Measurement, and Pain Assessment in Clinical Trials (IMMPACT) recommendations that support the importance of physical functioning as the core outcome for pain (19) this randomized controlled clinical trial (Calabria Region Ethics Committee protocol N.244 of 09/21/2021) will be the pilot forming the rational basis for the assessment of the efficacy in the use of ARAMIS to prevent chronic poststroke pain development. In fact, according to our working hypothesis, proprioceptive inputs with high-intensive bilateral movement training of the hemiplegic arm can prevent chronic poststroke pain development within the 3–6 months following stroke.

### Trial Design

This randomized single-center trial will recruit subacute hemiplegic patients of any age with hemiparesis of the arm after stroke. The trial is designed as a prospective, exploratory, and interventional study without drugs. The study does not request the use of drugs. This study protocol follows the Standard Protocol Items: Recommendations for Interventional Trials (SPIRIT) Checklist (20).

## Methods

This trial has been approved by the Calabria Region Ethics Committee (protocol N.244 of 09/21/2021) and the ClinicalTrials.gov ID has been requested. According to the D.lgs 196/2003, the Helsinki agreements and subsequent amendments, the Good Clinical Practice and current legislation, the Guidelines for the treatment of personal data in clinical trials of 24 July 2008, and in accordance with European data protection legislation, each participant or his/her legal representative will be required to sign a consent form as acceptance of all aspects of the study contained in the patient information sheet and as a consequent expression of his willingness to participate in the study. The information sheet will be duly illustrated to the subjects or legal representatives by the study staff and the same staff will ensure that the consent form is properly signed and dated by all the parties involved before any procedure foreseen by the protocol is carried out.

### Study Setting

The study will be carried out at the Sant' Anna Institute of Crotone (Calabria, Italy), which is specialized in motor and cognitive treatment and rehabilitation of neurological diseases.

### Eligibility Criteria

Consecutive patients, admitted to Sant' Anna Institute with the diagnosis of stroke after hospital discharge will be enrolled, accordingly with the following inclusion criteria:

- First-ever stroke within 24–72 h from diagnosis confirmed through functional MRI scan, regardless of the side, location, and extension of the lesion;-Stroke-related hemiplegic patients of any age at hospital discharge within 48–72 h after stroke with fMRI scan of the area affected;-Severe upper limb impairment, according to the Upper Extremity Subscale of the Fugl–Meyer Motor Assessment [FMA-UE (0-35) (21)];-Absence of hemiplegic upper limb-related baseline pain based on the visual analog scale (VAS), the bedside active examination with a numerical rating and, also, the douleur neuropathique en 4 questions (DN4) for the evaluation of neuropathic prestroke pain.

Exclusion criteria will be:

-Bilateral impairment;-Presence of aphasia;-Presence of cognitive impairment, as assessed using the cognitive assessment scale for patients with stroke (22), to avoid interference of aphasia or hemispatial neglect that may occur with the commonly used Mini-Mental State Examination (23) and Montreal Cognitive Assessment (24);-Stroke diagnosis without the occurrence of hemiparesis of the upper limb;-Previous rehabilitation.

Due to the lack of specific observational tools for poststroke pain in noncommunicative patients, this pilot study will not include patients affected by aphasia and cognitive impairment. The informed consent will be obtained by healthcare operators and patients will be informed about the study and they will be provided with a consent form. No additional consent provisions for biological specimens will be needed since the latter will not be collected.

